#### Definition of Adverse Event

**Adverse Event:** International Conference on Harmonisation (ICH) guideline E6(R1) defines an AE as any untoward medical occurrence in a clinical investigation subject administered a pharmaceutical product regardless of its causal relationship to the study treatment. An AE can therefore be any unfavorable and unintended sign (including any clinically significant abnormal laboratory finding), symptom, or disease temporally associated with the use of medicinal (investigational) product. The occurrence of an AE may come to the attention of study personnel during study visits and interviews or by a vaccine recipient presenting for medical care.

All AEs must be graded for severity and relationship to study product. Adverse events characterized as intermittent require documentation of onset and duration of each episode.

**Severity of Event:** All AEs will be assessed by a licensed clinician (*i.e.* medical doctor, nurse practitioner, or physician's assistant) using a protocol-defined grading system. For events not included in the protocol-defined grading system, the following guidelines will be used to quantify severity.

- Mild: events require minimal or no treatment and do not interfere with the subject's daily activities;
- Moderate: events result in a low level of inconvenience or concern with the therapeutic measures. Moderate events may cause some interference with functioning;
- Severe: events interrupt a subject's usual daily activity and may require systemic drug therapy or other treatment. Severe events are usually incapacitating; or
- Life-threatening: Any adverse drug experience that places the subject in the view of the Investigator, at immediate risk of death from the reaction as it occurred, ie, it does not include a reaction that had it occurred in a more severe form, might have caused death.

**Relationship to study products/vaccines:** The investigator's assessment of the relationship of an AE to study drug/vaccine is part of the documentation process, but it is not a factor in determining what is or is not reported in the study. If there is any doubt as to whether a clinical observation is an AE, the event should be reported. All AEs must have their possible relationship to study vaccine assessed using the following terms: associated or not associated. In a clinical trial, the study product must always be suspect. To help assess relationship, the following guidelines are used.

- **Associated** – There is a suspicion that there is an association between the study product and the AE, the event is temporally related to the administration of the study product, and no other etiology explains the event.
- **Not Associated** – There is no suspicion that there is an association between the study product and the AE, the event is temporally independent of the study product; and/or the event appears to be explained by another etiology.

### Local Reactions – Injection Site Reactogenicity

Reactogenicity events are AEs that are known to occur with this type of vaccine. Reactogenicity will be analyzed using the following grading systems:

| Local Reaction       | Mild (Grade 1)                                 | Moderate (Grade 2)                      | Severe (Grade 3)                  |
|----------------------|------------------------------------------------|-----------------------------------------|-----------------------------------|
| Pain/Tenderness      | Does not interfere with activity               | Interferes with activity                | Prevents daily activity           |
| Erythema/Redness*    | >0 – 5 cm and does not interfere with activity | 5.1 – 10 cm or interferes with activity | >10 cm or prevents daily activity |
| Induration/Swelling* | >0 – 5 cm and does not interfere with activity | 5.1 – 10 cm or interferes with activity | >10 cm or prevents daily activity |
| Ecchymosis/Bruising* | >0 – 5 cm and does not interfere with          | 5.1 – 10 cm or interferes with activity | >10 cm or prevents daily activity |

|  |          |  |  |
|--|----------|--|--|
|  | activity |  |  |
|--|----------|--|--|

\* Will be measured at the greatest single diameter

### Systemic Reactogenicity Events

Systemic events include signs, symptoms, and laboratory tests. These may be solicited or spontaneously reported. Grading of systemic events are as follows:

Systemic Signs: An axillary temperature of 37.5C is considered fever in adults. Fever severity will be graded as follows:

|       | Mild (Grade 1)                | Moderate (Grade 2)                | Severe (Grade 3) |
|-------|--------------------------------------|------------------------------------------|-------------------------|
| Fever | 37.8C (100°F) -
38.4°C (101.1 °F) | 38.5°C (101.2 °F) -
38.9°C (102.1 °F) | >38.9°C (102.1 °F)      |

### Systemic symptoms

The following grading system will be used in evaluating the subjective systemic events:

| Reaction | Mild (Grade 1)            | Moderate (Grade 2) | Severe (Grade 3) |
|-----------------|----------------------------------|---------------------------|-------------------------|
| Headache        | Does not interfere with activity | Interferes with activity  | Prevents daily activity |
| Malaise         | Does not interfere with activity | Interferes with activity  | Prevents daily activity |
| Myalgia         | Does not interfere with activity | Interferes with activity  | Prevents daily activity |
| Chills          | Does not interfere with activity | Interferes with activity  | Prevents daily activity |
| Nausea          | Does not interfere with activity | Interferes with activity  | Prevents daily activity |
| Vomiting        | Does not interfere with activity | Interferes with activity  | Prevents daily activity |

**Laboratory testing:** Laboratory testing will be performed on the specified study days and graded according to the scale listed in Appendix B.

### **Serious Adverse Event**

An SAE is defined as an AE meeting one of the following conditions:

- Results in death during the period of protocol defined surveillance.
- Is life threatening (defined as a subject at immediate risk of death at the time of the event).

- Requires inpatient hospitalization or prolongation of existing hospitalization during the period of protocol defined surveillance.
- Results in congenital anomaly or birth defect.
- Results in a persistent or significant disability/incapacity.
- Any other important medical event that may not result in death, be life threatening, or require hospitalization, may be considered an SAE when, based upon appropriate medical judgment, the event may jeopardize the subject and may require medical or surgical intervention to prevent one of the outcomes listed above.
- Examples of such medical events include allergic bronchospasm requiring intensive treatment in an emergency room or at home, blood dyscrasias or convulsions that do not result in inpatient hospitalization, the development of drug dependency or drug abuse or a diagnosis of HIV infection.

## 9.2 Reporting Procedures

Solicited local and systemic reactions and spontaneously reported adverse events will be captured on the appropriate CRF.

Information to be collected for spontaneous AEs includes event description, date of onset, investigator assessment of severity, investigator assessment of relationship to study product, date of resolution of the event, seriousness, and outcome. The severity of non-serious AEs may be assessed by a licensed clinician (i.e., medical doctor, nurse practitioner, physician's assistant) listed on the Form FDA 1572. The causal relationship of non-serious AEs can be assessed by a licensed clinician (i.e. medical doctor, nurse practitioner, physician's assistant). All AEs occurring while on study will be documented appropriately regardless of relationship to the Study Vaccine. All AEs will be followed to adequate resolution.

Any medical condition that is present at screening will be considered as baseline and will not be reported as an AE. If the severity of any preexisting medical condition increases during the study period, then it will be recorded as an AE.

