## **7 STUDY SCHEDULE**

### **7.1 Screening Day -42 to -1, Visit 1**

- Potential subjects will be provided with a verbal description of the study (purpose and study procedures), and will be asked if they have any questions and to read/sign the consent form. The consent form will be signed prior to the performance of any study procedures.
- The study staff will discuss with the subject his/her medical history, study eligibility criteria and concomitant medication use.
- Vital signs (axillary temperature, blood pressure, pulse) will be obtained.
- A PE will be performed by the investigator (lymph nodes, lungs, heart, liver, spleen) including height and weight. A complete neurologic examination will also be performed, to include assessment of central nerve function, motor function, sensory function, and deep tendon reflexes.
- For females who are capable of bearing children, a urine pregnancy test will be done at screening.
- A 20-mL blood sample will be collected from an arm vein to screen for health as follows:
  - Hematology: hemoglobin (Hgb), white blood cell count (WBC) with machine differential, absolute neutrophil count (ANC), and platelet count.
  - Chemistry: glucose, electrolytes (sodium, potassium), alanine aminotransferase (ALT), aspartate aminotransferase (AST), and creatinine.
  - Serology: HIV, HCV, and HBsAg.
- A urine sample will be obtained for urinalysis.

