### **7.2 Enrollment/Baseline Day 0, Visit 2**

- Eligibility criteria will be reviewed with subjects. Vital signs (axillary temperature, blood pressure, pulse) and interim medical history will be obtained.
- A targeted PE will be performed if indicated by the medical history.
- Concomitant medications will be recorded.
- A urine pregnancy test will be performed, and negative results, within 24 hours prior to vaccination, will be confirmed on all females of childbearing potential.
- A 50-mL blood sample for humoral and cell-mediated immune assays will be collected from a vein in the arm prior to vaccination.

- A thick smear slide will be prepared from the 50ml blood sample and will be stored to be read for parasitemia at a later time if necessary. Refer to section 8.2.1
- Enrolled subjects will be assigned to receive Ad35.CS.01 vaccine or normal saline placebo control using the dosage specified by their group (A→D, sequentially).
- Subjects will be observed in the clinic for a minimum of 30 minutes following vaccination. After 30 minutes, the vaccination site will be examined, vital signs will be obtained, and the subject will be questioned about the presence of any localized or generalized reactogenicity symptoms.
- Any spontaneous AEs that occur will be assessed.
- Subjects will be informed that a field worker will be visiting them at home every day (other than scheduled clinic visit day) for 14 days post each vaccination to record all medical information.
- Subjects will be instructed to return to the study center if they feel febrile on any individual day or if they develop any severe reactions following vaccination.

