| Immunogenicity Assays (50 mL blood), thick smear blood slide (days 0, 28 & 84) |                     | X |    |   |   |    | X  |    |    |    |    | X  | X  |     |    |    |    |     | X   |     |     |     |     |
| Concomitant Medications                                                        | X                   | X | X  | X | X | X  | X  | X  | X  | X  | X  | X  | X  | X   | X  | X  | X  | X   | X   | X   | X   | X   | X   |
| Vaccination                                                                    |                     | X |    |   |   |    | X  |    |    |    |    |    | X  |     |    |    |    |     |     |     |     |     |     |
| Assessment of Reactogenicity                                                   |                     | X |    | X | X | X  | X  |    | X  | X  | X  | X  | X  |     | X  | X  | X  | X   | X   |     |     |     |     |
| Adverse Event Assessment                                                       |                     | X | X  | X | X | X  | X  | X  | X  | X  | X  | X  | X  | X   | X  | X  | X  | X   | X   | X   | X   | X   | X   |
| Home visit for AE assessment                                       |                     |   | X  |   |   |    |    | X  |    |    |    |    |    | X   |    |    |    |     |     |     |     |     |     |
| HIV serology (5 mL blood) risk behavior and SAE assessment                     |                     |   |    |   |   |    |    |    |    |    |    |    |    |     |    |    |    |     |     |     |     |     | X   |

Screening activities must be completed within 42 days prior to Day 0.

A physical exam that assesses lymph nodes, lungs, heart, liver, and spleen will be performed on the screening visit; two and seven days post each vaccination; and thereafter if indicated by the subject's interim medical history. Height and weight will be measured at the screening visit.

Urine pregnancy tests will be required on all females of childbearing potential.

 $\beta$ -HCG: Urine pregnancy tests will be required for all female subjects of childbearing potential and must be within 24 hours prior to vaccination.

Home visits for Days 1-14 following each vaccination to assess AEs except for the scheduled clinic visit days

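### Section 9.2 fixes the adverse event baseline at screening, up to 42 days before dose 1, and never updates it at Day 0, so a few unsolicited events can be left out or wrongly recorded

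*Protocol*

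**What the plan says.** Section 9.2 of the protocol gives the baseline rule: "Any medical condition that is present at screening will be considered as baseline and will not be reported as an AE". The next sentence is its only exception: "If the severity of any preexisting medical condition increases during the study period, then it will be recorded as an AE". The same section sets the scope of collection: "All AEs occurring while on study will be documented appropriately regardless of relationship to the Study Vaccine". It does not say when being on study, or the study period, begins.

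The timing comes from the heading of Section 7.1, "Screening Day -42 to -1, Visit 1", and from a footnote to Appendix A: "Screening activities must be completed within 42 days prior to Day 0". Section 7.2 labels Day 0 as the enrolment and baseline visit and states that "Vital signs (axillary temperature, blood pressure, pulse) and interim medical history will be obtained". No section makes that Day 0 history the reference point for AEs.

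Two other places bear on when an AE can start. The AE definition in Section 9.1.1 reads: "any untoward medical occurrence in a clinical investigation subject administered a pharmaceutical product regardless of its causal relationship to the study treatment". In Appendix A, the row "Adverse Event Assessment" is blank at Visit 1 and has its first mark at Visit 2, Day 0.

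**The concern.** The usual reference for an AE is the subject's state just before the first dose. Here it is the state at a visit that may be six weeks earlier. A change in health during the gap can therefore put a condition on the wrong side of the line in either direction.

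The two directions differ in consequence. An event that is wrongly recorded can be found later, because Section 9.2 collects the onset date of spontaneous AEs. An event that the site was told not to report leaves no AE record, no grade and no causality assessment, and no analysis can bring it back. This is a collection rule, so it has to be right in the protocol.

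The primary objective is safety, and Section 9.1 assesses safety by AE frequency in each dosage group. With 10 vaccinees per group, a single event shows in the table.

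**Working it through.** The plan states no figure to reproduce. The check sets the two sentences of Section 9.2 against concrete cases.

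**Length of the gap.** The earliest screening day is -42 and dosing is on Day 0, so the gap is 0 - (-42) = 42 days at most.

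**Cases** (invented for illustration)

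1. *Unsolicited rash, Grade 1 at screening, gone by Day 0, back at Grade 1 on Day 3.* It was present at screening, so the first sentence makes it baseline. Against its screening grade, severity has not increased, so the exception does not apply. Literal result: not reported. The exception names no comparator; measured against its absence on Day 0, the same rash would be an increase.

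2. *Non-acute complaint that starts about Day -20 and continues unchanged after dose 1.* It was not present at screening, so the baseline rule does not exempt it. The Day 0 AE assessment in Appendix A will meet it but has no rule for classifying it. Result: it could be recorded as an AE although it began before dosing.

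3. *Condition mild at screening, moderate from Day -10, unchanged after dosing.* Severity rose in a study period whose start is undefined. Result: it could be recorded as an AE although nothing changed after vaccination.

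4. *Headache at screening, gone by Day 0, back on Day 1.* Headache is a solicited symptom in Section 9.1.1, collected for 14 days after each vaccination and captured on its own form. Nothing says that the baseline sentence suppresses solicited collection. Result: captured.

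5. *Cough that starts on Day -5 and is still present on Day 0.* Exclusion 15 in Section 5.4 covers acute illness in the week before vaccination, and Section 7.2 reviews eligibility on Day 0. Result: the subject would largely be kept from dosing that day, so the case seldom arises.

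The defect is therefore confined to cases 1 to 3: unsolicited conditions that change between screening and Day 0 and are not acute illness in the last week.

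**Weight of one event.** Each group has 10 vaccinees, so one misclassified vaccinee moves that group's proportion by 1/10 = 10 percentage points. The protocol plans 4 × 2 = 8 placebo recipients, so one of them moves the pooled placebo proportion by 1/8 = 12.5 points.

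**Primary outcome.** Section 3.2.1 counts spontaneous events only if they are Grade 3 and associated with vaccination. In case 1 a same-grade recurrence reaches Grade 3 only if the condition was already Grade 3 at screening, which the requirement of good health in Section 5.3 makes unlikely. In cases 2 and 3 the guidance on association looks for a temporal link and the absence of another explanation, and a pre-dose onset weighs against both.

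**The case against.** The other side is strong on size. Section 5.4 also excludes anyone with an abnormal screening laboratory value or a history of acute or chronic medical conditions, so few subjects carry a condition into the trial. The rule is the same in every group, so no differential effect between dosages is shown. Recorded onset dates let pre-dose onsets be separated, and a treatment-emergent rule of that kind may sit in an SAP that is not shown here. All of this stands and limits the effect. It does not help case 1, where no record is made.

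Three stronger readings are tempting, and the documents do not support them.

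- *A reader might infer that illnesses starting before dosing count as AEs.* The AE definition needs a subject who has been given the product, and Appendix A starts AE assessment on Day 0. Calling one set of conditions baseline does not make every other pre-dose condition an AE. Section 9.2 is out of line with those two places and leaves the matter open.

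- *A reader might infer that recurrences of screening conditions can never be counted.* Section 9.2 records any increase in severity, and going from absent on Day 0 to present afterwards can be read as one. Section 9.1.1 also tells sites to report when in doubt. What remains is a literal reading that excludes the event and an ambiguity that a site may resolve either way.

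- *A reader might put a number on it from assumed illness rates.* With 1 to 4 minor episodes per person-year lasting 5 to 10 days, the expected number of subjects ill at dose 1 runs from 48 × 1 × 5/365 = 0.7 to 48 × 4 × 10/365 = 5.3. The rates and durations are assumptions, and such short illnesses are mostly the ones that exclusion 15 keeps out. The range should not be used as an estimate of false AEs.

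**Conclusion.** The point holds as a defect in a collection rule, with a small effect. The baseline is set at screening, up to 42 days before dose 1, and is not brought up to date with the history taken on Day 0. Some unsolicited recurrences after vaccination are not reportable on a literal reading, and some complaints that start or worsen before dosing could be recorded as AEs.

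The number of events cannot be computed from the protocol. It is likely to be small and the events mostly low grade, given the exclusions and the separate capture of solicited symptoms. The exposure is in the overall frequency of unsolicited AEs by dosage group, with little effect on the primary outcome of associated Grade 3 events. The conclusion assumes that sites apply Section 9.2 as written and that solicited symptoms are collected whatever was present at screening. The change is still worth making, because safety is the primary objective and an event that is not reported cannot be recovered in analysis.

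**What to change.** Reword Section 9.2 to say three things:

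- Baseline is the subject's status immediately before the first vaccination, that is, the screening history updated by the Day 0 interim history.
- AE collection starts at the first vaccination.
- A condition that starts, recurs after having resolved, or worsens after the first vaccination is recorded as an AE.

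This brings Section 9.2 into line with the AE definition in Section 9.1.1 and with Appendix A, and it gives the severity exception a clear comparator.

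The cost is one or two sentences. No visit, procedure or form is added, because the Day 0 interim history is already taken. The downside is slightly more AE records from recurrences that would otherwise have been left out.

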### 9.2.1 Serious Adverse Event Detection and Reporting

All SAEs will be:

- Assessed for severity and causal relationship by a physician listed on the Form FDA 1572 as the principal investigator (PI) or subinvestigator.
- Recorded on the appropriate SAE report form.

- Assessed by an Independent Safety Monitor (ISM) that will share his/her assessment with DMID.
- Followed through resolution by a study physician.
- Reviewed by the safety monitor, the SMC (periodic review unless associated), DMID, and the IRB.

Any AE considered serious by the PI or subinvestigator or that meets the aforementioned criteria must be submitted on an SAE form to DMID Pharmacovigilance Group, at the following address:

**Questions about SAE reporting may be referred to the SAE Hotline at [contact].**

In addition to the SAE form, selected SAE data fields must also be entered into the EMMES Corporation AdvantageEDCSM web-based data entry system. Refer to the Manual of Procedures for details regarding this procedure. Timelines for submission of an SAE form are as follows:

- All deaths and life-threatening events, regardless of relationship, will be recorded on the SAE form and sent by fax within 24 hours of site awareness of the death or event.
- All other SAEs, regardless of whether they are associated or not, need to be reported to DMID within 24 hours of you becoming aware of them.

Other supporting documentation of the event may be requested by the pharmacovigilance contractor and should be provided as soon as possible.

All SAEs will be followed until satisfactory resolution or until the PI or subinvestigator deems the event to be chronic or the subject to be stable.

